## Abstract

**Background:**

Community-based recovery-oriented mental health services for people with severe mental disorders have not been fully implemented in Bulgaria, Croatia, Macedonia, Montenegro, and Romania. The RECOVER-E project facilitates the implementation of specialized mental health care delivered by setting up services, implementing the services, and evaluating multidisciplinary community mental health teams. The outcomes of the RECOVER-E project are assessed in a trial-based outcome evaluation in each of the participating countries with a health-economic evaluation linked to these trials.

**Objective:**

The aim of this protocol paper is to describe the methodology that will be used for the health-economic evaluation alongside the trials.

**Methods:**

Implementation sites have been selected in each of the five countries where hospital-based mental health services are available (care as usual [CAU]) for patients with severe mental disorders (severe depression, bipolar disorder, schizophrenia, and other psychotic disorders). The newly implemented health care system will involve community-based recovery-oriented mental health care (CMHC). At each site, 180 consenting patients will be randomized to either CAU or CMHC. Patient-level outcomes are personal and social functioning and quality-adjusted life years (QALYs). Data on participants’ health care use will be collected and corresponding health care costs will be computed. This enables evaluation of health care costs of CMHC as compared with CAU, and these costs can be related to patient-level outcomes (functioning and QALY gains) in health-economic evaluation.

**Results:**

Data collection was started in December 2018 (Croatia), February 2019 (Montenegro), April 2019 (Romania), June 2019 (North Macedonia), and October 2019 (Bulgaria). The findings of the outcome evaluations will be reported for each of the five countries separately, and the five trials will be pooled for multilevel analysis on a combined dataset.

**Conclusions:**

The results of the health-economic evaluation of the RECOVER-E project will contribute to the growing evidence base on the health and economic benefits of recovery-oriented and community-based service models for health systems in transition.

**Trial Registration:**

(1) ClinicalTrials.gov NCT03922425 (Bulgaria); https://clinicaltrials.gov/ct2/show/NCT03922425 (2) ClinicalTrials.gov NCT03862209 (Croatia); https://clinicaltrials.gov/ct2/show/NCT03862209 (3) ClinicalTrials.gov NCT03892473 (Macedonia); https://clinicaltrials.gov/ct2/show/NCT03892473 (4) ClinicalTrials.gov NCT03837340 (Montenegro); https://clinicaltrials.gov/ct2/show/NCT03837340 (5) ClinicalTrials.gov NCT03884933 (Romania); https://clinicaltrials.gov/ct2/show/NCT03884933

**International Registered Report Identifier (IRRID):**

DERR1-10.2196/17454

## Introduction

Many European countries have undergone the process of deinstitutionalization of their mental health care services. Often, this entailed a shift away from hospital-based care toward assertive community treatment (ACT) or ACT-like services for patients, such as flexible assertive community treatment (FACT). Under FACT models, patients live in the community and receive care from community mental health care teams (CMHTs) [1,2]. Typically, these teams consist of psychiatrists, psychologists, social workers, psychiatric nurses, and peers (people with lived experiences of severe mental disorders). The CMHTs focus on evidence-based (ie, guideline concordant) and patient-centered care in those domains where the patient needs recovery the most. This could be treatment directed at symptomatic remission, but could also, and just as importantly, entail support for the patient’s personal and social role functioning (eg, independent living, getting along with others, and participating in the community). In brief, the care offered by CMHTs can be described as community-based recovery-oriented models of care.

Community-based recovery-oriented mental health services for people with severe mental disorders are in the early stages of development in Bulgaria, Croatia, Macedonia, Montenegro, and Romania. The RECOVER-E project facilitates the implementation of specialized mental health care delivered by setting up services, implementing the services, and evaluating multidisciplinary CMHTs [3]. This implementation process is flanked by research from start to end. The outcomes of the RECOVER-E project are assessed in a trial-based *outcome evaluation* in each of the participating countries or sites (note that CMHTs will be used at the specified sites and not at the country level). An aspect of this outcome evaluation is the implementation of five health-economic evaluations designed alongside hybrid effectiveness-implementation trials. Finally, this outcome evaluation will result in a series of policy briefs to inform all stakeholders of the *policy dialogues* directed at national scale up of the newly implemented mental health care model and its sustainability.

The aim of this protocol paper is to describe the overall methodology of the five health-economic evaluations that will assess the incremental cost-effectiveness of CMHTs focusing on recovery-oriented care compared with care as usual (CAU). The economic evaluation will be conducted as both a cost-effectiveness analysis (CEA), where treatment response (defined as improvement in global functioning) is the primary outcome, and a cost-utility analysis (CUA) with quality-adjusted life years (QALYs) gained as the main outcome.

## Methods

### Design

The study is conducted at five sites in the cities of five countries in Central and Eastern Europe (Sofia, Bulgaria; Zagreb, Croatia; Skopje, Macedonia; Kotor, Montenegro; and Siret, Suceava County, Romania). In each country, the study is designed as a health-economic evaluation alongside a pragmatic randomized trial in two parallel groups, comparing newly implemented community-based recovery-oriented mental health care (CMHC) with CAU. Measurements will be performed at baseline (*t_0_*) and at 12 and 18 months after baseline (*t_1_* and *t_2_*, respectively). A Consolidated Standards of Reporting Trials (CONSORT) flow diagram of the study is shown in Multimedia Appendix 1.

### Selected Study Sites

In each of the five countries, one implementation site is selected, using the following criteria: demonstrated a need from stakeholders to scale up community care for people with mental ill health through policy documents, political decisions, or statements made via EU platforms such as the Joint Action for Mental Health and Wellbeing (2012-2015); firm local leadership and support for implementation from local decision-makers; and a selection of sites that reflect the diversity of health systems in Europe, the different stages of transition within the deinstitutionalization process for mental health care, and the different human and technical resources available to start implementation of a community-based mental health project. The selected sites are Mental Health Centre Prof. N. Shipkoveski Ltd. (Sofia, Bulgaria), University Hospital Centre Zagreb (Zagreb, Croatia), University Clinic of Psychiatry (Skopje, Macedonia), Psychiatric Hospital Dobrota (Kotor, Montenegro), and Siret Psychiatric Hospital (Suceava, Romania).

The trials will not start at the same time across all implementation sites in order to avoid allocating resources to all five trials simultaneously. Instead, a pragmatic approach will be adopted by starting three of the trials at three implementation sites in year 1 of the project (Croatia, Montenegro, and Romania), based on the preparedness to start the trial and the readiness of local authorities and health care professionals to start the implementation. The remaining two sites in Bulgaria and Macedonia will start the trial in year 2.

### Eligible Participants

The study participants are consenting adults (aged 18-65 years) with severe mental illness defined as follows: (1) Patients making their first entry into the mental health care system (ie, first admissions without a prior treatment history) with a diagnosis of bipolar disorder, severe major depression, schizophrenia, schizophreniform, and schizoaffective disorder according to the International Statistical Classification of Diseases and Related Health Problems-10 (not in symptomatic remission and in need for continued care) and having severe limitations in personal and social role functioning according to the International Classification of Functioning, Disability and Health (not in functional remission and in need of coordinated care provided by community mental health teams); (2) Readmitted patients who have a treatment history but make a re-entry into the mental health care system (ie, readmissions; patients who make a fresh start with treatment for a new episode or recurrence of their disorder) on meeting the diagnostic criteria for the above-mentioned diagnoses.

Patients will be excluded from participation on presenting with somatic comorbidities (ie, dementia or other severe organic causes of brain damage that can decrease their capacity to consent and participate in the study) that require prolonged medical care in a hospital, undergoing incarceration, or presenting with a terminally ill condition, which makes it impossible to either randomize them to community-based care or precludes long-term follow-up assessments in the context of the study. Patients will preferably be excluded from participation when they have a prior treatment history longer than the past 12 months (ie, from the time of possible inclusion or visit to the participating centers), because a longstanding treatment history may confound or bias the evaluation of patient-level health outcomes.

### Recruitment

Patients will be recruited from the population being treated by specialized inpatient and outpatient mental health services participating in the study. Eligible patients expressing interest to participate will receive an introductory letter, a patient information leaflet explaining the study’s aims and procedures, and an informed consent form. Patients willing to participate in the study will be asked to sign and return the informed consent form. Patients who decline participation in the study will receive CAU. Each included patient receives a unique identification number for data collection and monitoring of patient flow into and through the trial. At each site, a minimum of 180 patients and a maximum of 200 patients need to be recruited.

In line with ethical requirements, any study participant can decide to withdraw from the study at any time. In addition, responsible clinicians can decide for individual patients to deviate (temporarily or permanently) from the intervention program. Their professional autonomy and responsibility remain. Nonetheless, data analysis will be conducted in agreement with the intention-to-treat (ITT) principle, where all randomized participants are analyzed in the condition to which they were randomized.

### Intervention Condition

The CMHTs provide mental health care within a locally adapted version of FACT (thereby still allowing for flexibility due to differences in team compositions and other site-specific practices), an evidence-based service delivery model for providing services to people with severe mental illness, to attain their recovery goals, as well as timely and appropriate psychiatric care in the event of a crisis. FACT provides flexible and intensive home-based treatment to people with severe mental illness and is an adapted form of ACT; the latter approach has been widely implemented in North America, Australia, and Europe [4]. ACT is particularly effective (both clinically and cost-wise) when targeted to high users of inpatient care and has been found to be acceptable in patients [4].

### Comparator or Control Condition

Patients randomized to the control condition will be provided CAU by their respective health care organizations and accompanied providers . The constituent of usual care across the implementation sites differs, but it is mostly offered as hospital-based outpatient care (delivered within the psychiatric hospital) and inpatient psychiatric care. None of the current implementation sites have well-functioning CMHTs that provide home treatment or crisis care in the community.

### Randomization and Masking

Eligible and consenting patients will be randomly allocated to either the intervention (receiving care provided by CMHTs) or usual care condition consisting of inpatient or outpatient mental health care (described above). An independent statistician, otherwise not involved in the trial, will carry out the randomization at each of the sites, with patients as the unit of randomization. Simple randomization with 1:1 allocation will be applied using a randomization website [5] for true random number generation. In this type of study (a hybrid implementation-effectiveness trial), it is not possible to conceal the randomization status from either clinicians or patients, and masking will therefore not be attempted.

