### Cost-Effectiveness Analysis

The CEA, with costs and WHODAS functioning as the primary outcomes, will be conducted in several steps.

First, WHODAS global functional disability will be computed using the scoring algorithm based on the item response theory as recommended by WHO [6]. This algorithm provides a per patient functional disability score between 0 and 100, with higher scores indicating greater disability.

Second, the sample characteristics at *t_0_* will be described to see if despite randomization, some baseline imbalances across conditions have occurred in prognostically relevant variables (ie, variables that are strongly correlated with the outcome). If this is the case, such variables will be used as covariates to make adjustments for the baseline imbalances. In the unlikely scenario where many potential confounders are found, covariate adjustments will be made more efficiently using inverse propensity score weighting, with w=1/p in the control group and w=1/(1-p) in the experimental group, where *w* is the weight and *p* is the propensity score (ie, the likelihood that a participant is in one condition rather than the other), and *p* will be estimated under a logistic model.

Third, dropout will be evaluated, and missing observations in WHODAS functioning at *t_1_* and *t_2_* will be imputed to permit ITT analysis. The imputation will be based on the predictors of outcome (for accuracy) and predictors of missing values (to adjust for possibly selective dropout). To handle missing data, single imputation using predictive mean matching embedded in nonparametric bootstraps of seemingly unrelated regression equations (SURE model) will be used. In a recent paper by Brand et al, single imputation nested in the bootstrap percentile method emerged as the method with the best statistical properties [20]. Predictive mean matching will be used to account for nonnormality of the data by imputing “real” observed values from similar cases instead of imputing regression estimates [21,22].

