## Results

Data collection was started in December 2018 (Croatia), February 2019 (Montenegro), April 2019 (Romania), June 2019 (North Macedonia), and October 2019 (Bulgaria). At the time of acceptance of this manuscript, the following numbers of participants were included at each site: 91 in Bulgaria, 165 in Croatia, 180 in Romania, 197 in Montenegro, and 190 in North Macedonia. All procedures are in accordance with the ethical standards of the ethics committees of the participating countries and with the 1964 Helsinki Declaration and its later amendments or comparable ethical standards. Informed consent will be obtained from all individual participants included in the study. The five trials have been registered separately for every site. The registration numbers on ClinicalTrials.gov are as follows: NCT03922425 (Bulgaria), NCT03862209 (Croatia), NCT03892473 (Macedonia), NCT03837340 (Montenegro), and NCT03884933 (Romania). The results from the various evaluations will be summarized in policy briefs (a part of the policy influencing strategies developed in each country) using clear and nontechnical wording. The policy briefs will inform decision-makers about the project findings during the final policy dialogue sessions (one per site). Papers reporting primary outcomes will be published in open-access journals and findings will be presented in other academic and scientific fora as per the RECOVER-E research dissemination strategy [30]. The first results describing the follow-up data are expected in 2021.

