## Discussion

### General Considerations

This study will examine the cost-effectiveness of recovery-oriented community mental health care for patients with severe mental disorders (the intervention implemented in the RECOVER-E project) compared with CAU in Bulgaria, Croatia, Macedonia, Montenegro, and Romania. Health-economic evaluations will be conducted alongside hybrid effectiveness-implementation trials at each of the five sites. In addition, a pooled analysis will be performed combining all trial data. It is hypothesized that the shift toward deinstitutionalization using a locally adapted form of flexible assertive community treatment results in the reduction of health care costs by avoiding expensive emergency care or psychiatric hospitalization. At the same time, this intervention has a focus within service delivery on recovery goals, which is hypothesized to contribute to a greater sense of societal role fulfilment and participation in society among people with severe mental illness. It is not unlikely that patients receiving community care will show larger improvements in WHODAS personal and social functioning and EQ-5D health-related quality of life as compared with patients treated in hospital-based mental health care services.

Given the nature of the intervention, a pragmatic approach is chosen to implement and evaluate community mental health services. While this may affect internal validity (eg, due to the lack of allocation concealment and masking), the corresponding results may be more generalizable and applicable to routine practice settings [31]. Moreover, the proposed methodology includes some methodological solutions to combat threats to the internal validity of the trials (eg, inverse propensity score weighting when randomization appears to be suboptimal).

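### The plan concedes a lack of allocation concealment as if open care made it unavoidable, and names propensity weighting, which cannot replace concealment, as an example solution

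*Protocol article*

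**What the plan says.** All places are in the protocol article.

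- **Methods, Randomization and Masking.** For this type of trial, "it is not possible to conceal the randomization status from either clinicians or patients, and masking will therefore not be attempted". The same section says that "An independent statistician, otherwise not involved in the trial, will carry out the randomization at each of the sites". It uses simple 1:1 randomization from a random-number website and describes the patients as already eligible and consenting when they are allocated.
- **Discussion, General Considerations.** The pragmatic approach may affect internal validity, for example "due to the lack of allocation concealment and masking". As an example of a methodological solution to such threats, the text gives "inverse propensity score weighting when randomization appears to be suboptimal".
- **Methods, Cost-Effectiveness Analysis.** Prognostic variables that are imbalanced at baseline become covariates. Weighting is the fallback: "In the unlikely scenario where many potential confounders are found, covariate adjustments will be made more efficiently using inverse propensity score weighting".
- **Methods, Eligible Participants.** One prognostic entry criterion is left to judgement: "Patients will preferably be excluded from participation when they have a prior treatment history longer than the past 12 months". The reason given is that a long treatment history could bias the evaluation of outcomes.
- **Methods, Measures.** The primary outcome is the self-reported WHODAS 2.0, with trained interviewers available to help patients who need it.
- **Results.** Numbers included when the article was accepted: "91 in Bulgaria, 165 in Croatia, 180 in Romania, 197 in Montenegro, and 190 in North Macedonia".

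**The concern.** Allocation concealment and masking are different safeguards. Concealment keeps the next assignment from the recruiter until the patient is irrevocably enrolled. Masking keeps the assignment from people afterwards. Open care rules out masking of patients and treating clinicians, but it has no bearing on concealment. The article treats the two together and presents the loss of both as a consequence of the pragmatic design.

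If concealment really is absent, a recruiter who knows the next assignment can act on an impression of prognosis that is recorded nowhere. A criterion that only preferably excludes patients gives room to do so. The resulting bias would enter both functioning and costs. Weighting and covariate adjustment balance what was measured, so they cannot repair selection on what was not.

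A second, smaller step in the reasoning is also too wide. That clinicians and patients cannot be masked does not mean that no masking is possible. Analysts can work on coded arms, and those who help with the primary questionnaire need not always be told the arm. This concerns detection bias; concealment would not cure it.

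**Working it through.** **1. The passages side by side.** Read alone, the sentence in Randomization and Masking may mean only that treatment is open after allocation. The Discussion removes that doubt about what is conceded, because it names allocation concealment and masking as two separate things and says both are lacking. Yet the procedure in Methods (independent statistician, no blocks to guess from, allocation after consent and eligibility) has most of what concealment needs. The article does not say whether assignments are withheld from recruiters until enrolment is final. Either the Discussion concedes a flaw that the procedure does not have, or the procedure lacks a safeguard that it could have.

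**2. The plan's own sample size.** Inputs from Sample Size Calculation: d = 0.33, two-sided alpha 0.05, power 0.80, one baseline and two follow-ups. The variance factor is (1 + r12)/2 − r01². In the worst cell of Table 1 (r01 = 0.3, r12 = 0.4) it is 0.70 − 0.09 = 0.61, and n = 2 × (1.960 + 0.842)² × 0.61 / 0.33² ≈ 88 per arm, as stated. All nine cells reproduce. Power at 90 per arm in that cell is 0.809. Concealment would not change these figures.

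**3. How large a bias could be (assumed inputs).** Let b be the prognostic imbalance, in SD units, left after adjustment. If a net fraction f of patients is steered with a prognosis gap of g SD, then b = f × g: 0.10 × 0.5 = 0.05; 0.10 × 1 = 0.10; 0.20 × 1 = 0.20. Against the target effect, 0.05/0.33 = 15%, 0.10/0.33 = 30% and 0.20/0.33 = 61%.

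With no true effect, the two-sided false-positive rate is 1 − Φ(1.96 − b/SE) + Φ(−1.96 − b/SE), where SE = √(variance factor × 2/n). For 90 per arm, SE = 0.1164 in the largest-variance cell of Table 1 (factor 0.61) and 0.0882 in the smallest (0.60 − 0.25 = 0.35). For 450 per arm, SE = 0.0521 and 0.0394.

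| Assumed b (SD) | One trial, 90 per arm | Pooled, 450 per arm |
|---|---|---|
| 0 | 0.05 | 0.05 |
| 0.05 | 0.07 to 0.09 | 0.16 to 0.25 |
| 0.10 | 0.14 to 0.21 | 0.48 to 0.72 |
| 0.20 | 0.40 to 0.62 | 0.97 to 1.00 |

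The pooled column ignores clustering by site and assumes the same b at every site. It shows that pooling shrinks random error but not a shared bias.

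**4. What baseline adjustment removes.** It removes the part of the imbalance carried by baseline WHODAS. Under the plan's own r01 of 0.3 to 0.5, the baseline score explains 0.3² = 9% to 0.5² = 25% of the variance at 12 months, so most of the variation in outcome lies outside it.

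**5. Who a procedural change can still reach.** To 180 per site, Bulgaria needs 180 − 91 = 89 and Croatia 180 − 165 = 15, together 104. Already included: 91 + 165 + 180 + 197 + 190 = 823. So 823 of 927 (89%) were already in. This takes inclusion to mean randomization and assumes that both sites reach 180.

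**The case against.** The strongest reply is that Methods already describes a sound procedure. An independent statistician allocates patients who have consented and been found eligible, and simple randomization offers no pattern to predict. On that view the Discussion phrase is loose wording in a limitations paragraph. The article also condenses a central study protocol, mentioned under Data Handling, which may fix when assignments are released. Much of this stands: concealment may exist in practice, and silence on release timing would not by itself be a fault. It does not dispose of the point, because the article states outright that concealment is lacking, and that statement is either wrong or describes an avoidable weakness.

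Two stronger readings are tempting. A reader might infer that recruiters knew upcoming assignments and that the trials are therefore biased. No part of the article says so. A reader might also infer that the analysis relies on propensity weighting in place of concealment. The Cost-Effectiveness Analysis section makes ordinary covariate adjustment the first step and weighting a fallback, the Discussion offers weighting only as an example, and the article never claims that it corrects unmeasured selection.

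On masking, the stated reason mentions only clinicians and patients. The article does not say who employs the interviewers, and someone helping a patient who knows the arm may easily learn it. Interviewer masking is therefore worth attempting only where staffing permits.

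**Conclusion.** The point holds as an avoidable risk and an inconsistency to be reconciled, not as demonstrated bias. Concealment is achievable with the statistician already planned, and neither weighting nor covariate adjustment can make up for its absence. The discretionary treatment-history criterion matters only if assignments can be foreseen, which the article concedes in principle and does not show in fact. Any size is an assumption: a residual imbalance of 0.05 to 0.20 SD would be about 15% to 60% of the 0.33 SD target, and pooling would make such a bias more likely to reach significance. The sample size is unaffected. Because most patients were already included, reporting what happened matters as much as changing the procedure.

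**What to change.** - Reconcile Randomization and Masking with General Considerations, treating concealment and masking as separate matters.
- Have the independent statistician release each allocation only after consent, the eligibility decision (including the treatment-history criterion) and baseline WHODAS, EQ-5D and cost data are logged.
- Code the arms for the analyst. Where existing staff allow, use WHODAS interviewers from outside the treating team who are not told the arm.
- Report by site whether concealment held for patients already randomized.
- Remove the suggestion that propensity weighting makes up for absent concealment, and keep it as an adjustment for measured imbalance.

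The cost is mainly wording and procedure, since the statistician and the interviewers are already in the plan. The downside is a short delay between baseline and allocation. The release rule can help only patients still to be randomized; coded analysis and site-level reporting can apply to all.
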